## Abstract

Colonoscopy has been regarded as an important method of early diagnosing and treating gastrointestinal lesions; however adequate bowel preparation is critical one of many factors needed for successful colonoscopy. Although several modified or novel regimes have been developed, desired quality of bowel preparation has not yet been generated. Scattered evidences revealed that castor oil may have potential of effectively cleansing colon. It is noted that, however, prospective trial of exploring the value of castor oil in preparing bowel before colonoscopy is lacking. The aims of this study are to test the hypotheses that low dose castor oil (30 mL) may enhance potential of polyethylene glycol (PEG) and combination of low castor oil and ascorbic acid may halve the volume of PEG.

This is a randomized, double-blind (endoscopist and assessor), single center trial with three-arm design. We will randomly assign 282 adult patients (≥18 years but < 75 years), who are scheduled to undergo colonoscopy, to receive either 3 L PEG alone, 2 L PEG plus 30 mL castor oil or combination of 1 L PEG, 30 mL castor oil and 5 g ascorbic acid. The bowel preparation quality based on Boston Bowel Preparation Scale (BBPS) is the primary outcome. The secondary outcomes include the first defecation time, total number of defecation, time of cecal intubation, detection rate of polyp and adenoma, willing to repeat the same regime, tolerance to regime, and adverse events.

The study protocol has been approved by the Clinical Research Ethics Committees of Chongqing University Cancer Hospital & Chongqing Cancer Institute & Chongqing Cancer Hospital & Chongqing Cancer Center (2017[107]). The results from this trial will be submitted for publication in peer-reviewed journals, and will be presented at national and international conferences.

## Introduction

1

Colorectal cancer (CRC) remains one of the most prevalent cancers in both sexes worldwide^[1]^ and is also the critical contributor to high cancer-related morbidity and mortality.^[2]^ Colonoscopy has been regarded as the important method of early detecting CRC and effectively treating gastrointestinal lesions.^[3]^ Evidences suggest that the mortality of CRC will be approximately reduced by 50% if polyps and abnormal lesions in digestive tract were early detecting and endoscopic resected.^[4,5]^ However, adequate bowel preparation is the prerequisite of effective and safe colonoscopy.^[6]^ Some studies reported that inadequate bowel cleansing is responsible for more than 40% of colonoscopy failures.^[7]^ Moreover, poor bowel preparation will also decrease the detection rate of polyp and adenoma,^[8]^ prolong the operation time,^[9]^ and increase the risk of procedure related complications and medical expenditure.^[10]^

In everyday practice, multiple factors will impair quality of colon cleans.^[11]^ Of those all factors, low patient compliance to, poor palatability of and required liquid of preparation solution account for 20% to 25% of inadequate bowel preparations.^[6]^ To date, a large number of modified or novel bowel preparation regimes such as split dose polyethylene glycol (PEG) and low-dose PEG plus ascorbic acid have been developed in order to obtain adequate bowel preparation.^[3]^ However, desired bowel preparation has not yet been obtained. It remains a changeling to optimize the bowel preparation efficacy prior to colonoscopy.

Castor oil is a safe, effective, and cheap laxative with highly efficacious for colon cleans,^[12]^ which has been widely used as the laxative in many settings such as intravenous urography.^[13–15]^ Apisarnthanarak et al^[12]^ found that castor oil and sodium phosphate (NaP) obtained similar patients’ satisfaction and efficacy of colon cleans for barium enema. The trial performed by Yang et al^[15]^ observed no difference in laxative efficacy between castor oil and bisacodyl for intravenous urography. It must be noted that, moreover, combination of bisacodyl and PEG^[16]^ and combination of NaP^[17]^ obtained promising bowel preparation efficacy, decreased the required volume of liquid, and improved the compliance with the recommended regime when compared to standard PEG regime. Moreover, the potential of 2 L PEG plus ascorbic acid is equal to that of 3 L PEG,^[18]^ and which is better than that of 2 L PEG plus NaP.^[19]^ And thus, we speculate that combination of 2 L PEG and castor oil may have similar potential with 2 L PEG plus bisacodyl or NaP for colon cleanses, and which is not inferior to the potential of 3 L PEG. More importantly, 2 trials^[20,21]^ found that combination of 1 L PEG, bisacodyl, and ascorbic acid improved the patient's tolerability and did not compromise bowel preparation efficacy compared with combination of 2 L PEG and ascorbic acid. So, we also speculate that combination of castor oil and ascorbic acid may have the potential of halving the required volume of PEG.

Published evidences^[22–24]^ suggested that large dose castor oil (50 or 60 mL) may be more likely to cause some adverse effects such as abdominal cramping, vomiting, nausea, abdominal fullness, fainting, and insomnia. However, some trial^[12]^ found that the incidence of adverse events in low dose castor oil (30 mL) is lower than that of NaP. So, we hypothesize that 30 mL castor oil may enhance potential of PEG, and combination of 30 mL castor oil and ascorbic acid (5 g)^[25]^ may halve the required volume volume of PEG.

## Methods and analysis

2

We developed this protocol according to the Recommendations for Interventional Trials (SPIRIT).^[26]^ The trial is registered at Chinese Clinical Trial Registry (www.chictr.org.cn) with identifier ChiCTR-IIR-17012418.

### Objectives

2.1

The aims of this trial are to investigate the potential of 30 mL castor oil in enhancing colon cleans and the role of combination of 30 mL castor oil and 5 g ascorbic acid in halving the required volume of PEG.

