#### Study protocol

2.3.5

According to the findings from our previous meta-analysis,^[27]^ all participants enrolled in the study will be instructed to take low fat and residue diet without food color the day before colonoscopy, and all begin to fast at 20:00 pm on the day before colonoscopy. Patients can allow eating bun, bread, and chocolate in order to enhance tolerance, decrease incidence of adverse events such as hypoglycemia and cardio-cerebral vascular accidents if they experienced serious hunger feeling.

The study protocols of all 3 groups were graphically depicted in Figure 2. According to the recommendation from US Multi-Society Task Force on Colorectal Cancer,^[28]^ we will instruct all patients to ingest bowel preparation regime with split-dose. So, the 3 L PEG alone group will be instructed to ingest 1 L of PEG at 20:00 to 21:00 PM on the day before colonoscopy and the remaining 2 L at the 3:00 to 5:00 AM on the morning before colonoscopy (Fig. 2A). The combination of 2 L and 30 mL castor oil group will be instructed to ingest 1 L of PEG and 30 mL castor oil at 20:00 to 21:00 PM on the day prior to colonoscopy and the remaining 1 L of PEG and extra 1 L clean water at the 3:00 to 5:00 AM on the morning before colonoscopy (Fig. 2B). The combination 1 L PEG, 30 mL castor oil and 5 g ascorbic acid group will be instructed to ingest 0.5 L of PEG, 30 mL castor oil and 5 g ascorbic acid and extra 0.5 L clean water at 20:00 to 21:00 PM on the day before colonoscopy and the remaining 0.5 L of PEG and extra 1.5 L clean water at the 3:00 to 5:00 AM on the morning before colonoscopy (Fig. 2C). The patients were instructed to digest PEG 250 mL every 15 minutes. Moreover, all eligible participants will be admitted to take oral 10 mL dyclonlne and 20 mL clean water at the 10 minutes prior to colonoscopy. For all eligible patients, propofol injection will be intravenously administered for sedation.

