## Discussion

3

Although several advanced treatments for CRC have been developed, CRC remains one of the common cancers worldwide.^[1]^ Although many noninvasive tests such as fecal immunochemical test, fecal occult blood test, and CT colonography are available,^[33]^ colonoscopy has been used a preferred method to early diagnosing CRC and treating gastrointestinal lesions,^[3]^ and the issued data suggested that the colonoscopy was associated with the decreased mortality of CRC.^[27]^ It is noted that, however, the inadequate bowel preparation will significantly decrease the effectiveness and safety of this given procedure.^[6]^ A numerous of regimes such as PEG, NaP, and sodium picosulphate with magnesium citrate have been developed to clean colon before colonoscopy,^[34]^ but the effectiveness of all these regimes are not still satisfactory.^[35]^ And thus, it is essential to develop novel bowel preparation regime.

Some published evidences suggested that 30 mL castor oil has the potential of enhancing colon cleans compared to NaP.^[12]^ Moreover, evidence also demonstrated similar laxative efficacy between castor oil and bisacodyl.^[15]^ However, it is unclear if 30 mL castor oil may enhance the potential of PEG prior to colonoscopy.

So we design the randomized, double-blind, single center with three-arm design to test whether 30 mL castor oil may enhance the potential of 2 L PEG and combination of 30 mL and 5 g ascorbic acid may halve the required volume of PEG. The results of the trial will influence evidence based decision making for bowel preparation regimen prescriptions as it will be fundamental in providing reliable recommendations for bowel preparation regimens before colonoscopy.

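### The objectives credit castor oil, and castor oil with ascorbic acid, with effects that the three arms can only compare as whole regimens

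*Protocol article*

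**What the plan says.** Objectives (2.1) gives two aims: the potential of 30 mL castor oil to improve cleansing, and "the role of combination of 30 mL castor oil and 5 g ascorbic acid in halving the required volume of PEG". The Discussion makes the first aim specific: the trial is designed "to test whether 30 mL castor oil may enhance the potential of 2 L PEG". The Introduction takes a different line on the same arm. It speculates that 2 L PEG with castor oil has a cleansing potential "which is not inferior to the potential of 3 L PEG".

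Study protocol (2.3.5) defines what patients drink. The control takes 1 L PEG in the evening and 2 L in the morning. The second arm takes 1 L PEG and castor oil in the evening, then "the remaining 1 L of PEG and extra 1 L clean water at the 3:00 to 5:00 AM". The third arm takes 0.5 L PEG, castor oil, ascorbic acid and 0.5 L water in the evening, then "the remaining 0.5 L of PEG and extra 1.5 L clean water".

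Sample size calculation (2.3.3) assumes adequate preparation in 85%, 90% and 95% of the three arms and is framed as detecting a difference. Statistical analysis (2.3.7.6) compares groups by two-tailed tests, with a chi-square test for the primary outcome.

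**The concern.** Both aims are worded as component effects: what castor oil does to PEG, and what castor oil with ascorbic acid does to the PEG volume needed. A component effect needs two arms that differ only in that component. If no such pair exists, no analysis can supply it, so this is not a detail that a statistical analysis plan could settle.

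What is at stake is the conclusion. The Discussion expects the results to inform prescribing. A conclusion that castor oil enhances PEG, or that the combination halves PEG, would go further than the randomised comparison does, even if the trial runs exactly as planned.

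**Working it through.** **1. Contents of each arm**, added up from Study protocol (2.3.5):

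| Arm | PEG | Water | Total fluid | Castor oil | Ascorbic acid |
|---|---|---|---|---|---|
| 1 | 1 + 2 = 3 L | 0 L | 3 L | no | no |
| 2 | 1 + 1 = 2 L | 1 L | 3 L | yes | no |
| 3 | 0.5 + 0.5 = 1 L | 0.5 + 1.5 = 2 L | 3 L | yes | yes |

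**2. What each pair changes:**

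- Arm 2 vs arm 1: 1 L PEG is replaced by water, and castor oil is added. PEG ratio 2/3.
- Arm 3 vs arm 1: 2 L PEG is replaced by water, and both additives are added. PEG ratio 1/3.
- Arm 3 vs arm 2: 1 L PEG is replaced by water, and ascorbic acid is added; castor oil is in both. PEG ratio 1/2.

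Pairs that vary castor oil at a fixed PEG volume: 0 of 3.

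**3. First aim.** Let R(P, c) be the adequate-preparation rate with P litres of PEG made up to 3 L with water, with castor oil (c = 1) or without (c = 0). Then

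R(2,1) − R(3,0) = [R(2,1) − R(2,0)] + [R(2,0) − R(3,0)].

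The left side is arm 2 minus arm 1. The first bracket is the castor oil effect that the Discussion asks about. R(2,0) is not observed, so the two brackets cannot be separated. The documents give no value for R(2,0). Taking 75%, 80% or 85% as an assumption, and the planned 90% for arm 2, the castor oil effect would be 90 − 75 = 15, 90 − 80 = 10 or 90 − 85 = 5 percentage points. In all three cases the trial would see the same arm difference, 90 − 85 = 5 points.

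**4. Second aim.** Half of the control's PEG is 3/2 = 1.5 L, and no arm has that. Arm 3 has 1/3. The halving pair (arm 3 vs arm 2) keeps castor oil constant, so it bears on replacing 1 L PEG by ascorbic acid and water, not on the two additives together. The precedent cited in the Introduction has a different structure: 1 L PEG with bisacodyl and ascorbic acid against 2 L PEG with ascorbic acid. There, ascorbic acid was common and the laxative differed; here, castor oil is common and ascorbic acid differs.

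**5. The indirect route to the first aim.** If more PEG never worsens cleansing, then R(2,0) ≤ R(3,0), and the castor oil effect is at least the arm 2 minus arm 1 difference. A clear win for arm 2 would then support a castor oil effect. The chance of such a win, with n = 255/3 = 85 per arm (equal allocation assumed; the ratio is not stated) and two-sided 5% (the printed 0.05% is read as 0.05, in line with the P < .05 threshold in Statistical analysis), is

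power = Φ{[√n·|p₂ − p₁| − 1.96·√(2p̄(1 − p̄))] / √(p₁(1 − p₁) + p₂(1 − p₂))}.

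With p₁ = 0.85, p₂ = 0.90 and p̄ = 0.875: [0.461 − 0.917]/0.466 = −0.98, so power is about 16%.

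**6. Type of claim.** The Introduction expects arm 2 to be no worse than 3 L PEG. The sample size section assumes it is 5 points better and looks for a difference. Non-inferiority would show that castor oil and water can stand in for 1 L PEG. It would not show enhancement: with an arm difference of zero or below, the bound in step 5 no longer lies above zero.

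**The case against.** The strongest reply is that the trial is a regimen-replacement trial and should be read as one. The Introduction's rationale for arm 2 is replacement, and arm 2 vs arm 1 tests exactly that. Arm 3 vs arm 2 is an exact 2 L to 1 L halving. The 2 L wording stands in the Discussion, not in the Objectives, and a win for arm 2 despite less PEG would point to castor oil. All of this stands. A reader might infer that the objectives cannot be answered at all, or that no pair halves PEG; the documents do not support either reading. What the reply does not rescue is the attribution. The halving pair cannot credit castor oil. The inference from a win rests on an assumption that the protocol does not state, and has about a 16% chance of arising at the protocol's own rates.

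A second tempting reading is that equal 3 L intake defeats the purpose, since the Introduction lists "low patient compliance to, poor palatability of and required liquid of preparation solution" among the causes of poor preparation. That goes too far. The stated aim concerns PEG volume, which does vary (3, 2 and 1 L), and equal fluid removes total volume as a confounder. Replacing PEG by water may still change palatability and compliance. The protocol does not claim that its own arms reduce total liquid, so predicting such a report would be speculation.

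Leaving the water out of the short arm names is ordinary shorthand, because section 2.3.5 gives the volumes in full. It is a minor matter and does not carry this point.

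**Conclusion.** The concern holds as a fault in how the objectives and conclusions are worded, not in the choice of arms. None of the three pairs isolates castor oil. The combination arm has one third of the control's PEG where the aim says half. The only halving pair has castor oil on both sides. These statements follow from the volumes in section 2.3.5 and need no further assumption.

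The 16% figure is supporting evidence only. It depends on equal allocation, 85 analysed per arm and the assumed 85% and 90%.

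**What to change.** Keep the arms. Restate the objectives and the conclusions they permit as named whole-regimen contrasts:

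1. 2 L PEG, castor oil and 1 L water vs 3 L PEG.
2. 1 L PEG, castor oil, ascorbic acid and 2 L water vs 3 L PEG, described as a two-thirds reduction in PEG.
3. Arm 3 vs arm 2 as the halving contrast, read as replacing 1 L PEG by ascorbic acid and water on a castor oil background.

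For each, state whether superiority or non-inferiority is claimed, so that the Introduction and the sample size section agree; a non-inferiority claim needs its margin fixed before data are seen. Do not conclude that castor oil itself enhances PEG; a win in contrast 1 may be called indirect support, with its assumption stated. Say that the results concern PEG volume and not total liquid.

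The cost is narrower claims. The rewording alters no treatment, visit or enrolment number.

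For scale only, and not as a proposal: isolating castor oil directly would take a comparator with arm 2's PEG volume and no oil. With 90% in arm 2, two-sided 5% and 80% power, that contrast would need 100, 199 or 686 per arm before dropout if the comparator's rate were 75%, 80% or 85% (assumed, as in step 3 of the working). Rewording is the proportionate remedy.

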### Trial design and setting

2.2

This randomized, double-blind (endoscopist and assessor), single center trial with three-arm is designed to explore the potential of 30 mL castor oil in preparing bowel prior to colonoscopy. We will enroll and randomly assign all eligible candidates to receive either 3 L PEG, combination of 30 mL castor oil, and 2 L PEG or combination of 30 mL castor oil, 5 g ascorbic acid and 1 L PEG (see Fig. 1). This study will be conducted in the Departments of Gastroenterology of Chongqing University Cancer Hospital & Chongqing Cancer Institute & Chongqing Cancer Hospital in Mainland China.

**Figure 1 F1:**
[figure not shown]
Flowchart of the study. Asc = ascorbic acid, CaO = castor oil, PEG = polyethylene glycol.

### Participant selection

2.3

#### Inclusion criteria

2.3.1

Participants will be enrolled if the following criteria were met: age above 18 and under 75 years; adult outpatients who will be scheduled to undergo morning colonoscopy regardless of sex; did not participate in other clinical trials which also aimed at investigating bowel preparation efficacy; and agree to participate, and give signed written informed consents.

#### Exclusion criteria

2.3.2

We will exclude those patients if any of the following criteria were met: lactation; pregnancy; experienced the abdominal surgery such as gynecogic surgery, appendectomy, and laparoscopy; neurological diseases; contraindication of colonoscopy, allergy to ingredients of PEG, castor oil or ascorbic acid or medically vulnerable populations (decompensated liver disease, chronic heart failure, known renal diseases or glomerular filtration rate [GFR] < 30), socially vulnerable populations such as prisoners and incapable of consent, patients with high risk for preparation failure such as narcotic use, chronic constipation, past inadequate preparation, and known gastrointestinal motility disorders.

#### Sample size calculation

2.3.3

The bowel preparation efficacy will be primarily tested, and thus we will calculate the anticipated sample size based on this given outcome. According to the findings from the previous studies,^[18,20]^ we propose that the rate of adequate bowel preparation in 3 L PEG, combination of 2 L PEG and 30 mL castor oil, and combination of 1 L PEG, 30 mL castor oil and 5 g ascorbic acid will be 85%, 90%, and 95%. We assumed the significance and power to be 0.05% and 80%, respectively, and thus the sample size required to detect difference will be 255 patients. Because the dropout rate is expected to be 10%, totally 282 patients should be enrolled.

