#### Recruitment, randomization, and blinding

2.3.4

The day before colonoscopy, investigators who have been trained for the study and are authorized by the principal investigator will assess candidates according to the inclusion and exclusion criteria. After eligible patients were identified, the written informed consents will be obtained from the eligible patients, their next of kin or legal representatives. At the phase, the investigators will also collect demographic and clinical characteristics data of all eligible patients, which includes sex, age, body weight, body mass index, reasons for colonoscopy, previous colonoscopy history, and comorbidity such as hypertension, diabetes mellitus, and cardiovascular disease.

All recruited patients will be randomly assigned to receive one of the 3 preparation regimes including 3 L PEG, combination of 2 L PEG and 30 mL castor oil, and combination of 1 L PEG, 30 mL castor oil, and 5 g ascorbic acid. We will generate the random sequence by using SPSS 17.0 software, and the random sequence will be sealed in opaque envelope. An independent research nurse will be designated to random all patients into 3 different groups according to the random sequence.

In order to eliminate the risk of bias as much as possible, the endoscopists will be blinded except the research nurse who conducted the randomization procedure during examine period. Moreover, we will also blind the biostatistician.

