##### Statistical analysis

2.3.7.6

In this study, we will adopt intent-to-treat (ITT) and per-protocol (PP) method to analyze all data. Demographic and clinical characteristics will be summarized with means, medians, and standard deviations. To assess differences between groups, data will be analyzed with Mann–Whitney *U*-test, Student's *t* test and Chi-square test according to the variables evaluated. Differences between groups regarding the bowel preparation efficacy will be analyzed with the Chi-square test. We will perform the subgroup analyses according to the indication for colonoscopy and previous history of colonoscopy. It is noted that all statistical analyses will be conducted with 2-tailed test, and *P* values of < .05 will be considered as considered significant. All statistical analyses will be performed by blinded professional statisticians with SPSS ver. 17.0 for Windows (SPSS Inc., Chicago, IL).

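### Section 2.3.3 prints the sizing significance level as 0.05%, contradicting the two-tailed P < .05 rule in 2.3.7.6; it is most likely a unit slip, and the printed sample size cannot confirm which level was used

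*Protocol article*

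**What the plan says.** Section 2.3.3 sizes the trial on the rate of adequate bowel preparation, planned at 85% with 3 L PEG, 90% with 2 L PEG plus castor oil, and 95% with 1 L PEG plus castor oil and ascorbic acid. It continues "We assumed the significance and power to be 0.05% and 80%, respectively" and draws from this that "the sample size required to detect difference will be 255 patients". A 10% dropout allowance takes the total to 282.

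Section 2.3.7.6 covers the analysis. For the primary outcome, "Differences between groups regarding the bowel preparation efficacy will be analyzed with the Chi-square test". For everything, "all statistical analyses will be conducted with 2-tailed test" and P "values of < .05 will be considered as considered significant". It names no stricter level for the primary outcome. Neither section describes 0.05% as adjusted for multiple comparisons.

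**The concern.** The significance level appears twice in the article with two values, and it is an input to the stated sample size. A level of 0.05% is 0.0005; a level of .05 is 5%. Both cannot describe the same primary comparison.

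The statement is wrong as written; nothing here depends on material left to a fuller document. The percent sign stands in running prose, so a broken table does not explain it.

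The stake is whether the sizing can be traced. Anyone checking or reporting the calculation needs to know the level behind it, and the one printed beside it is not the level at which the trial will test. Normally the intended value can be recovered by repeating the calculation. The working shows that this fails here.

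**Working it through.** **Inputs.** From 2.3.3: rates 0.85, 0.90 and 0.95; power 80%; 255 patients before dropout and 282 after. From 2.3.7.6: two-tailed testing, P < .05, chi-square test. From 2.3.4: three arms. The allocation ratio is not given; I assume equal arms, which fits 255 = 3 × 85 and 282 = 3 × 94. The article does not say whether the chi-square test is one overall comparison or a set of pairwise ones, so I show both.

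**The two levels.** 0.05% = 0.0005, and 0.05 / 0.0005 = 100.

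**Trying to reproduce 255: overall 3 × 2 chi-square test, 2 df.**
- Mean rate = 0.90.
- Effect size: w² = mean[(p − 0.90)²] / (0.90 × 0.10) = [(0.0025 + 0 + 0.0025) / 3] / 0.09 = 0.01852.
- Total N = λ / w², where λ is the noncentrality giving 80% power.
- At 5%: critical value 5.99, λ = 9.63, N = 520.3, so 521.
- At 0.05%: critical value 15.20, λ = 21.36, N = 1,153.5, so 1,154.

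**Trying to reproduce 255: pairwise, 85% versus 95%, the widest planned difference.**
- n per arm = [z(α/2) √(2 × 0.90 × 0.10) + z(β) √(0.85 × 0.15 + 0.95 × 0.05)]² / 0.10², with z(β) = 0.842.
- The two square roots are √0.18 = 0.4243 and √0.175 = 0.4183.
- At 5%, z = 1.960: (0.8315 + 0.3521)² / 0.01 = 140.1, so 141 per arm and 423 over three arms.
- At 0.05%, z = 3.481: (1.4768 + 0.3521)² / 0.01 = 334.5, so 335 per arm and 1,005 over three arms.

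**Side by side (total over three arms, 80% power).**

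| Test | N at 5% | N at 0.05% | Power of 255 at 5% | Power of 255 at 0.05% |
|---|---|---|---|---|
| Overall, 2 df | 521 | 1,154 | 48% | 6% |
| 85% vs 95% | 423 | 1,005 | 59% | 9% |

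The other two pairs need more. At 5%, 90% versus 95% needs 435 per arm and 85% versus 90% needs 686 per arm.

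**Other variants.** One-sided tests, continuity correction, unpooled variance, the arcsine method and a trend test do not give 255 over three arms at either level. Neither do non-inferiority formulas with margins of 5, 10 or 15 points, which are my assumption because the article states no margin. Working backwards, 255 patients would have 80% power only at a level of about 0.27 (overall test) or 0.18 (85% versus 95%).

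Two near-matches do not help. For two arms only, 85% versus 95% at 5% gives 260 (one-sided, continuity-corrected) or 282 (two-sided). The article has three arms and two-tailed tests, and gives 282 as the total after dropout.

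**Dropout step.** 85 × 1.1 = 93.5, rounded to 94 per arm, gives 282. Dividing instead, 255 / 0.9 = 283.3, so 284. This step is close enough and is not where the problem lies.

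**The case against.** The strongest reply is that this is a self-evident misprint. Section 2.3.7.6 is the only decision rule. It names the chi-square test for bowel preparation efficacy and then puts all analyses at two-tailed P < .05. Section 2.3.3 records a planning assumption, not a threshold for declaring success. Correcting the figure changes no patient, test or conclusion. The shortfall that matters, 423 to 521 needed against 255, exists at 5% whatever is printed in 2.3.3.

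Most of this stands, and it rules out three stronger readings.

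- A reader might infer that the threshold for the primary claim is undecided, so that P = .01 would be positive under one section and negative under the other. The documents do not support that: by 2.3.7.6, P = .01 is significant.
- A reader might infer that 255 was computed at 0.0005. Only the wording links them. At that level 255 patients would have about 6% power by the overall test.
- A reader might take the roughly 2.2-fold ratio of 1,154 to 521 as the damage done. It is not, because nothing suggests that anyone sized the trial at 0.0005.

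The reply does not make the printed figure right. It is a stated design parameter that conflicts with the analysis section, and the printed sample size does not reveal the value intended.

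**Conclusion.** The contradiction is real and lies in the text: 0.05% in 2.3.3 against two-tailed P < .05 in 2.3.7.6, a factor of 100. The likely explanation is a percent sign attached to a proportion, with 5% intended. That is an inference from the analysis rule, since 255 matches neither level.

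The sample size ranges rest on equal arms, the 85%/90%/95% rates, 80% power, and either an overall 2-df test or an 85% versus 95% comparison carried over three arms. They show that the sample size cannot identify the level used; they do not measure harm from the misprint. The point is a definite error in a core design parameter, with limited consequence because the decision rule is clear. The low power at 5% is a separate and larger problem.

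**What to change.** In 2.3.3, replace 0.05% with a two-sided significance level of 0.05 (5%), so that it agrees with 2.3.7.6. State any revised power or sample size at that level, and name the comparison it refers to.

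The level correction costs one figure. It adds no patients and leaves the analysis and the decision rule in 2.3.7.6 as they are. It should not be presented as resolving the sample size: at 5%, 255 remains below the 423 to 521 computed above, and that needs its own answer.

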##### Primary outcome

2.3.7.1

The bowel preparation efficacy was regarded as the primary outcome, which will be assessed by using the Boston Bowel Preparation Scale (BBPS). As one of the commonest scales of assessing quality of bowel preparation,^[29]^ the BBPS evaluates right (including the cecum and ascending colon), transverse (including the hepatic and splenic flexures), and left (including the descending colon, sigmoid colon, and rectum) colon on a 4-point scoring system with a total score out of 9.^[30]^ In this scoring system, a score of 9 was summed if the whole colon was perfectly cleaned without any residual liquid, and a score of 0 was calculated if colonoscopy is impossible.^[31]^ The adequate bowel preparation was defined as having total score > 5 and no segment < 2 in the present study.^[32]^ The direct endoscopists will be trained to use the BBPS to grade the quality of bowel preparation during colonoscopy.

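### The stated 80% power is not delivered: at 85%/90%/95%, 255 patients give about 48% power for a three-arm chi-square test and 16% for 2 L plus castor oil versus 3 L PEG

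*Protocol article*

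**What the plan says.** Section 2.3.3 (Sample size calculation) sets the expected rates of adequate preparation at 85% for 3 L PEG, 90% for 2 L PEG plus castor oil, and 95% for 1 L PEG plus castor oil and ascorbic acid. It continues: "We assumed the significance and power to be 0.05% and 80%, respectively", and "thus the sample size required to detect difference will be 255 patients". Dropout is then added: "Because the dropout rate is expected to be 10%, totally 282 patients should be enrolled".

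The endpoint behind these rates is binary. Section 2.3.7.1 states: "The adequate bowel preparation was defined as having total score > 5 and no segment < 2". For its analysis, section 2.3.7.6 states: "Differences between groups regarding the bowel preparation efficacy will be analyzed with the Chi-square test". The same section makes all tests two-tailed, with significance at P < .05.

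The article gives no allocation ratio, sample size formula, target contrast or non-inferiority margin.

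**The concern.** The section prints a complete set of inputs (rates, power, significance level) and an output (255), and the analysis section supplies the test and its sidedness. The claim can therefore be checked, and 255 looks far too small. Differences of 5 points near 90% normally need several hundred patients per arm, and even the 10-point difference between the outer arms needs well over 85.

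This calculation is the only justification for the size of the trial on its primary outcome. If it is wrong, the trial is likely to miss the benefit it assumes. A non-significant result would then be given the weight of a finding from an adequately powered study. The discussion section expects the results to support reliable recommendations on bowel preparation, so that misreading would have consequences.

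**Working it through.** **Inputs.**
- Rates 0.85, 0.90, 0.95; power 80%; N = 255 evaluable, 282 enrolled (section 2.3.3).
- Chi-square test, two-sided, P < .05 (section 2.3.7.6).
- Assumptions, because the article does not state them: 1:1:1 allocation, so 255/3 = 85 per arm (282/3 = 94 if nobody drops out), and one overall three-arm comparison (3 × 2 table). Pairwise contrasts are checked as well.

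**1. Can 255 be reproduced?** No. One- and two-sided tests, pooled and unpooled variance, continuity correction, the arcsine formula, a trend test, adjusted significance levels and 90% power were all tried. None that is consistent with a three-arm, two-tailed test of difference gives 255. Two near matches need premises that the article does not contain:
- 3 × 86 = 258, for one-sided 5% non-inferiority with a 5-point margin and rates of 90% and 95%.
- 2 × 130 = 260, for a two-arm, one-sided, continuity-corrected comparison of 85% with 95%.

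The dropout step is not the problem: 255/0.9 = 283.3 and 282 × 0.9 = 253.8, a rounding difference.

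**2. Three-arm chi-square test, 2 degrees of freedom.**
- Mean rate = 0.90.
- w² = mean of (pᵢ − 0.90)² / (0.90 × 0.10) = [(0.0025 + 0 + 0.0025)/3] / 0.09 = 0.01852.
- Noncentrality at N = 255: λ = 255 × 0.01852 = 4.72.
- Power from the noncentral chi-square distribution at 5%: **48.0%** (simulation with 400,000 trials: about 48%).
- At N = 282: λ = 5.22, power 52% (simulated 53%).
- 80% power needs λ = 9.63, so N = 9.63/0.01852 ≈ 520.3, or **about 521** (522 with equal arms).

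**3. Pairwise contrasts, two-sided 5%.** Required n per arm = [1.96·√(2p̄(1−p̄)) + 0.84·√(p₁(1−p₁) + p₂(1−p₂))]² / (p₁−p₂)², where p̄ is the mean of the two rates. Power at 85 per arm is the exact power of the uncorrected chi-square test.

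| Contrast | Power at 85 per arm | n per arm for 80% |
|---|---|---|
| 85% vs 90% | 16.4% | 686 |
| 85% vs 95% | 60.3% | 141 |
| 90% vs 95% | 22.5% | 435 |

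The normal approximation gives 16.4%, 58.6% and 23.4%, which leads to the same conclusion. With all 282 evaluable (94 per arm), the best contrast reaches 65%.

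**4. What the design can detect.** With 85 per arm and 85% in the 3 L group, exact power is 77% against an arm at 96.5% and 82% against an arm at 97%. About 97% is therefore the rate that can be detected with 80% power.

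**5. Does the allocation assumption matter?** In a grid of unequal splits with at least 5% of patients in each arm, the three-arm test reached at most about 66%. Putting all 255 patients into the two outer arms gives only about 76–77% for 85% versus 95%.

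**6. The printed 0.05%.** Taken literally (0.0005), three-arm power at 255 is about 6% by formula (4.5% simulated), and about 1,154 patients would be needed.

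**The case against.** The strongest reply is that the article names neither a 1:1:1 split nor a three-arm table. It gives a total and says only that a chi-square test will be used, so both the 48% and the 16% refer to a structure supplied by the reader. That is fair as to labelling, and both are marked as assumptions above. It does not rescue the figure: no allocation and no pairwise contrast reaches 80% with 255 patients.

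A second reply is that the intended question is non-inferiority, which the introduction mentions for the 2 L regimen. There it is background speculation. No margin is given, the calculation is framed as detecting a difference, and the planned tests are two-tailed.

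A third is that 0.05% is a misprint for 5%. Very probably so. The main figures here already take the 5% reading, and the literal one only worsens the result.

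Finally, a condensed article may leave the formula and target contrast to the full protocol. That excuses their absence. It does not excuse printed inputs and a printed output that disagree. It is also true that nobody can be sure how readers would take a null result, so that part of the consequence is a judgement.

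**Conclusion.** The sample size statement is wrong as written. At two-sided 5% with 85 per arm, power is about 48% for the three-arm chi-square test (52–53% if all 282 are evaluable). For the contrasts with 3 L PEG it is 16% for 2 L plus castor oil and 60% for 1 L plus castor oil and ascorbic acid. The three-arm test would need about 521 evaluable patients for 80% power, roughly twice the number planned. The exact percentages assume equal allocation, but the conclusion that 80% is not reached does not. Separately, the 0.05% in section 2.3.3 contradicts the 5% level in section 2.3.7.6.

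**What to change.** Keep the 282 patients and correct section 2.3.3:

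- Change 0.05% to 5%, two-sided.
- State the allocation ratio and the contrast that the calculation is for.
- Replace 80% with the actual power: 48% for the three-arm test, 16% and 60% for the two contrasts with 3 L PEG, and a detectable rate of about 97% against 85%.

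The cost is a rewritten paragraph and a less favourable stated power.

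If 80% power for the three-arm test is wanted instead, the trial needs about 522 evaluable patients, or 522/0.9 = 580 enrolled.

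If the primary hypothesis is recast as non-inferiority, the power for that hypothesis should be stated. The margin would be new, because the article gives none. As an illustration, with a 10-point margin and one-sided 2.5%, 85 per arm give 84% power if the true rates are 90% versus 85%, and 99% if they are 95% versus 85%. Both rely on the new regimens being truly better: if both arms are at 85%, power is only about 45%, and that figure should be shown beside the others.
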